Caregivers seeking health information for their children have reported using the internet as their main source of information and reported high levels of confidence [25], and individuals seeking health information will most often use mobile devices [26]. However, a review of websites on infant health promotion including infant feeding found that the quality, accessibility and readability of the information was poor or adequate [27], highlighting the need for the development of interventions for caregivers and HCPs to be evidence-based, appropriate and useable.

The Public, Patient, Involvement and Engagement (PPIE) group who informed the development of this funding application suggested that any intervention around responsive feeding should utilise digital technology. Therefore, this research aims to develop an app to deliver a behaviour change intervention to caregivers. The chosen approach is a Reusable Learning Object (RLO) which consists of an interactive format with audio, text, animations and videos to promote health behaviour change. To this end, this research will co-create a RLO with caregivers to promote responsive feeding.

The aim of this study is to develop a RLO for caregivers of infants under one year to increase awareness, understanding and use of responsive infant feeding behaviours (CRIB). Improving responsive feeding will contribute to the prevention of obesity at an individual and population level. In addition, this study aims to develop infographic guidance for HCPs and support workers to use with caregivers alongside the RLO.

Objectives:To co-design a RLO to increase caregiver awareness, understanding and use of responsive infant feeding behaviours.To create an infographic for HCPs and support workers to improve their knowledge and ability to support caregivers with responsive feeding.To conduct an initial evaluation of the acceptability of the RLO for caregivers and the guidance infographic for HCPs and support workers.To determine the care pathways within the NHS, social care enterprises and the local authority where the RLO will be offered to caregivers with appropriate support.

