### 2.3. Data Collection

This project will take place in the city of Nottingham, UK. Nottingham City has high levels of social deprivation and minority ethnic groups. It ranks 11th most deprived out of the 317 districts in England [31]. According to the 2021 census, 65.9% of Nottingham residents identified their ethnic group within the White category, 14.9% identified within the Asian category, 10.0% within the Black category and 5.9% within the Mixed or Multiple category, with the remaining 3.3% identifying within the Other group [32].

Recruitment to workshops (phases 1 and 3)

We will recruit participants from two groups to the workshops. These participants will include caregivers (parents, guardians and carers) of healthy infants ≤ 1 year of age, and HCPs working with caregivers (health visitors and infant feeding leads) and support workers (family mentors from Small Steps Big Changes (SSBC)). SSBC is a programme of work under the national lottery-funded Better Start Scheme (https://www.smallstepsbigchanges.org.uk/) that provides support to caregivers in the most socioeconomically deprived areas of Nottingham. To maximise engagement and to minimise attrition, we will offer potential participants shopping vouchers to cover their childcare costs, taxis to and from the venue and lunch. The workshops will take place in a child-friendly environment with space for caregivers to take time out and with changing facilities. Participants will be asked to participate in all four workshops, which will take place in phase 1 and phase 3.

*Caregivers.* The sample will consist of caregivers (parents, guardians and carers) ≥ 18 years of age who are the main carer of an infant < 1 year of age at the time of recruitment. Caregivers will be recruited via SSBC. NICE guidance refers to the need to include people with all perspectives and skills for co-design rather than a specific number [33]. These are face to face workshops and it is vital that all voices are heard; we will recruit up to ten caregivers to ensure all participants can contribute meaningfully to the discussions. We will aim for maximum variation in gender, age, socioeconomic background and ethnicity and will use a sampling frame to ensure representation.

Family mentors from SSBC who wish to support recruitment will display a study poster and offer the participant information sheet to potential stakeholders. Family mentors will pass on the contact details of participants to the RA.

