The following caregivers are excluded from the study:<18 years of age;Infant age > 1 year;Has an infant who is not fed orally (nasogastric or parental nutrition);Has an infant with a condition(s) likely to impact their ability to feed, since this impacts on how caregivers feed their infants and the supports needed;Caregivers who do not have access to digital technology.

*HCPs and support workers.* The RLO will be developed by caregivers for other caregivers. We are also keen to include the perspectives of HCPs (health visitors, infant feeding leads and family support workers) in the workshops to contribute to our understanding of what might be possible in relation to the provision of infant feeding advice in the NHS and social care. HCPs will be recruited from local NHS trusts, SSBC and social care enterprises. We will aim for at least one representative health visitor, infant feeding lead and family support worker to attend our workshops.

The following HCPs (and support workers) are excluded from this study.

HCPs/support workers who are not working with caregivers of infants <1 year of age.

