##### Recruitment for Evaluation

We will conduct a preliminary evaluation of the functionality, acceptability and usability of the RLO. Caregivers, HCPs and support workers (who were not part of the RLO development) will be recruited for either a formative survey or one of two summative surveys. Potential participants will be emailed a link to the RLO, patient information sheet (PIS), informed consent form (ICF) and respective survey. Participants will be given up to two weeks to access and complete the surveys and will be able to work through the RLO as many times as they require during this two-week period.

Survey 1—Up to 20 caregivers, HCPs and support workers will be asked to review the prototype RLO for content and ease of use.

Survey 2—Up to 30 caregivers will be recruited via Small Steps Big Changes (https://www.smallstepsbigchanges.org.uk/) and public contributors.

Survey 3—Up to 30 HCPs and support workers will be recruited via contacts at the Institute of Health Visiting and the Royal College of Midwives and gatekeepers at local NHS trusts who will be asked to send the survey via email to HCPs and support workers.

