*Survey 1* (formative) responses will explore the usability of the RLO content and functionality and will be completed by caregivers, HCPs and support workers. The questions have been adapted from a survey tool by Johnson et al. exploring the usability of an e-learning resource to improve the knowledge and confidence of teachers working with children born pre-term [35]. Survey 1 (see Appendix A Table A1 survey A1) will consist of 9 closed questions with responses of agree, neutral or disagree to questions such as “the CRIB-RLO resource held my interest”.*Survey 2* (summative) (see Appendix A Table A2 survey A2) will be completed by caregivers and will ascertain the impact of the RLO on caregivers in terms of changing behaviours related to responsive feeding. There will be 7 closed questions on a 3-point scale from agree, neutral and disagree, including questions such as “The CRIB-RLO resource has improved my confidence in knowing how to feed my baby” and “The CRIB-RLO resource has increased my motivation to actively look for and respond to my babies cues during feeding”.*Survey 3* (summative) (see Appendix A Table A3 survey A3) will be completed by HCPs working with caregivers of infants and will explore the implementation of the RLO and infographic in practice within the NHS and other organisations. The questions have been developed based on a the Theoretical Framework of Acceptability (TFA) developed by Sekhon et al. [36]. The TFA can be used to evaluate the prospective and retrospective acceptability of healthcare interventions by both intervention deliverers and intervention participants. Preliminary reliability testing on the Sekhon et al. TFA adapted for examining the implementation of a telephone-assisted coaching framework revealed three main factors. These are affective attitude and effectiveness (Cronbach’s alpha 0.9, coherence and understanding (0.77), perceived burden (0.85), and suggesting an appropriate level of internal consistency for each construct [37].

Survey 3 will include a mixture of eight open and two closed questions on the implementation of the RLO in practice. Open questions include those such as “Can you describe any additional effort you might need to employ to implement the CRIB-RLO/Infographic into practice?” and closed questions such as “how prepared are you to deliver the CRIB RLO to caregivers?” with a 5-point Likert scale ranging from not at all prepared to highly prepared.

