##### Analysis

Survey responses will be downloaded to an Excel/Sav file.

Survey 1 responses evaluating RLO content, functionality and usability will be analysed with descriptive statistics in the form of frequencies and percentages. The data will be categorised to highlight areas of function or content that require amending.Survey 2 responses examining the impact and usefulness of the RLO on caregivers will be analysed with frequency tables and descriptive statistics. Data from the closed questions will be analysed to examine the impact of the RLO on changing behaviours related to responsive feeding.Survey 3 responses from HCPs exploring the implementation of the RLO and infographic will be a mixture of quantitative and qualitative data. The quantitative data from the two Likert scale questions will be analysed with frequency tables and descriptive statistics. The qualitative data gathered from the open questions will be analysed using content analysis [34].

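### Survey 3's named recruitment routes leave out SSBC and social care enterprises, so support workers and non-NHS settings may be under-represented in the only survey that asks about the infographic

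*Protocol article*

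**What the plan says.** Recruitment for Evaluation (section 2.3.4) gives the Survey 3 population as HCPs and support workers, at most 30 in all, who "will be recruited via contacts at the Institute of Health Visiting and the Royal College of Midwives and gatekeepers at local NHS trusts". The trust contacts are "gatekeepers at local NHS trusts who will be asked to send the survey via email to HCPs and support workers". Thirty is a ceiling, and no minimum is set for any group.

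Other parts of the article bear on who should be reached:

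- The Objectives at the end of the Introduction include an initial evaluation of the acceptability of "the guidance infographic for HCPs and support workers". The fourth objective is about care pathways in the NHS, social care enterprises and the local authority.
- For the workshops, section 2.3 describes the "support workers (family mentors from Small Steps Big Changes (SSBC" programme as participants and states that "HCPs will be recruited from local NHS trusts, SSBC and social care enterprises".
- The Method text says that Survey 3 "will be completed by HCPs working with caregivers of infants" and that it looks at implementation in the NHS and in other organisations. The Analysis text speaks of "Survey 3 responses from HCPs exploring the implementation of the RLO and infographic".
- Part 1 of Table A3 asks for the respondent's job, with a box for parent support workers. It also asks for the employer, with boxes that include a social enterprise, the local authority and charities or NGOs.

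**The concern.** The routes for Survey 3 are narrower than the population and settings it is meant to describe. They consist of one health visiting body, one midwifery body and local NHS trusts. The two routes that brought in SSBC and social care enterprise staff for the workshops are dropped. SSBC does appear in the line above, but only as a route to caregivers for Survey 2.

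Survey 1 also includes support workers, but its items concern the RLO only. Survey 2 goes to caregivers. If Survey 3 reaches few support workers, no other survey supplies their view of the infographic, and that part of objective 3 is thinly answered. The same holds for objective 4 if few respondents work outside the NHS. Section 2.1 makes no sample size calculation and relies instead on a broad, representative sample, so the recruitment routes have to deliver that breadth. Later analysis cannot supply the views of a group that was not reached.

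**Working it through.** The plan gives no calculation to reproduce for Survey 3. The check is a comparison of the routes with what the survey has to cover, followed by an illustration of size.

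**Step 1: routes against coverage**

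| Group or setting | Where the article calls for it | Workshop route (2.3) | Named Survey 3 route |
|---|---|---|---|
| Health visitors | Table A3 job list | Yes | Institute of Health Visiting |
| Midwives | Table A3 job list | Not named as a group | Royal College of Midwives |
| NHS trust staff | Objective 4; Table A3 | Yes | NHS trust gatekeepers |
| SSBC family mentors | Section 2.3 (the workshop support workers) | Yes, SSBC | None direct |
| Social care enterprise staff | Objective 4; Table A3 employer list | Yes | None direct |
| Local authority staff | Objective 4; Table A3 employer list | Not named | None direct |

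The last three rows have no direct Survey 3 route. The forwarding request to NHS trust gatekeepers may reach some of these people indirectly.

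**Step 2: which survey carries the infographic.** The Table A1 items are about the RLO. The Table A2 items are about the RLO and the caregiver's own feeding. Only Table A3 asks about the infographic.

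**Step 3: how many support workers might answer.** Input from the article: at most 30 respondents. Input assumed: a share p of support workers among those who answer, which the article does not give. Treating respondents as independent draws:

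- Expected number = n × p
- Chance of none = (1 − p)^n
- Chance of two or fewer = binomial probability of 0, 1 or 2 in n

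| n | p | Expected | None | Two or fewer |
|---|---|---|---|---|
| 30 | 5% | 30 × 0.05 = 1.5 | 0.95^30 = 0.21 | 0.81 |
| 30 | 10% | 30 × 0.10 = 3.0 | 0.90^30 = 0.04 | 0.41 |
| 30 | 20% | 30 × 0.20 = 6.0 | 0.80^30 = 0.001 | 0.04 |
| 15 | 5% | 15 × 0.05 = 0.75 | 0.95^15 = 0.46 | 0.96 |
| 15 | 10% | 15 × 0.10 = 1.5 | 0.90^15 = 0.21 | 0.82 |
| 15 | 20% | 15 × 0.20 = 3.0 | 0.80^15 = 0.04 | 0.40 |

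The rows with n = 15 are shown because 30 is only a ceiling. With 30 respondents, a very small number of support workers is plausible if their share is about 10% or less. At 20% it is unlikely.

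**The case against.** A reader might infer that the article contradicts itself on who is eligible, since Recruitment for Evaluation names HCPs and support workers while the Method text, the Analysis text and the title of Table A3 name HCPs alone. The documents do not support that. The Introduction counts support workers such as family mentors among HCPs, section 2.3 places family support workers in the same bracket, and the Survey 3 form has a box for them. This is loose terminology. It is worth tidying because the Method text does list the two groups separately for Survey 1.

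A reader might also infer that only support workers employed by NHS trusts can answer, or that none will. Neither follows. Gatekeepers are asked to pass the survey to support workers, nothing confines forwarding to trust employees, and the employer list shows that non-NHS respondents are expected. The article also does not say who employs the family mentors. It describes SSBC as a programme, and it identifies the mentors as support workers when describing the workshops.

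The strongest remaining defence is that this is a small exploratory survey without hypothesis tests, that support workers contribute to the workshops and to Survey 1, and that a condensed article may not list every gatekeeper. The first part limits the weight of the point. The second does not fill the gap for the infographic: the workshops precede its production, and Survey 1 does not ask about it. On the third, the article does specify the Survey 3 routes, and the specified set omits two that it names for the workshops.

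**Conclusion.** The point holds as a mismatch between Survey 3's named routes and the groups and settings that objectives 3 and 4, the workshop recruitment and the survey's own form call for. Support workers and non-NHS settings may be under-represented in the only survey that covers the infographic.

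The size cannot be fixed from the article. The figures above rest on an assumed share and on independent responses. They show that the risk is material at shares of 10% or less, or with a poor response, and small at 20% with the full 30. Under-representation is therefore a risk and not a certainty. It is worth correcting before recruitment because the correction is cheap.

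**What to change.** In Recruitment for Evaluation, add SSBC and social care enterprises as Survey 3 gatekeepers, and a local authority contact where one is available, keeping the cap of 30.

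In Analysis, tabulate respondents and the two closed items by the job question already in Part 1 of the form. Limit the conclusions on acceptability and implementation to the job groups and settings actually reached.

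As tidying only, write HCPs and support workers in the Survey 3 sentences of Method and Analysis and in the title of Table A3.

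The cost is a few more emails, a minor amendment, and somewhat fewer NHS trust or midwifery respondents under the same cap. SSBC and social care enterprises are already workshop routes. A local authority contact would be new, since it is not a named route elsewhere.

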##### Method

In the first step of the formative evaluation, public contributors, content experts and members of the healthy weight/healthy nutrition group at the Institute of Health Visiting will be asked to evaluate the proposed content to ensure that it is accurate. The public contributors include caregivers from a diverse range of backgrounds who have made different feeding choices (breast and/or formula). The RLO specification will be amended following this evaluation, and the content will be uploaded to the media platform. The prototype will be evaluated by public contributors to ensure that it is fit for purpose by looking at the fit between the content and media.

Next, an initial analysis will be conducted after completing the RLO through three online, anonymous surveys evaluating the acceptability and usability of the RLO. Participants will view and engage with the RLO, which typically takes 15–20 min, although they can review sections as many times as they wish. The anticipated time for completion of each survey is no more than 20 min.

*Survey 1* (formative) responses will explore the usability of the RLO content and functionality and will be completed by caregivers, HCPs and support workers. The questions have been adapted from a survey tool by Johnson et al. exploring the usability of an e-learning resource to improve the knowledge and confidence of teachers working with children born pre-term [35]. Survey 1 (see Appendix A Table A1 survey A1) will consist of 9 closed questions with responses of agree, neutral or disagree to questions such as “the CRIB-RLO resource held my interest”.*Survey 2* (summative) (see Appendix A Table A2 survey A2) will be completed by caregivers and will ascertain the impact of the RLO on caregivers in terms of changing behaviours related to responsive feeding. There will be 7 closed questions on a 3-point scale from agree, neutral and disagree, including questions such as “The CRIB-RLO resource has improved my confidence in knowing how to feed my baby” and “The CRIB-RLO resource has increased my motivation to actively look for and respond to my babies cues during feeding”.*Survey 3* (summative) (see Appendix A Table A3 survey A3) will be completed by HCPs working with caregivers of infants and will explore the implementation of the RLO and infographic in practice within the NHS and other organisations. The questions have been developed based on a the Theoretical Framework of Acceptability (TFA) developed by Sekhon et al. [36]. The TFA can be used to evaluate the prospective and retrospective acceptability of healthcare interventions by both intervention deliverers and intervention participants. Preliminary reliability testing on the Sekhon et al. TFA adapted for examining the implementation of a telephone-assisted coaching framework revealed three main factors. These are affective attitude and effectiveness (Cronbach’s alpha 0.9, coherence and understanding (0.77), perceived burden (0.85), and suggesting an appropriate level of internal consistency for each construct [37].

Survey 3 will include a mixture of eight open and two closed questions on the implementation of the RLO in practice. Open questions include those such as “Can you describe any additional effort you might need to employ to implement the CRIB-RLO/Infographic into practice?” and closed questions such as “how prepared are you to deliver the CRIB RLO to caregivers?” with a 5-point Likert scale ranging from not at all prepared to highly prepared.

For a long-term evaluation beyond the term of the project, it is standard practice for HELM to monitor RLO feedback from users through an optional short feedback survey at the end of the RLO. This will track ongoing usage and utility of the RLO. Since this survey is optional, Google analytics are also used to track global usage and reach.

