## 2. Materials and Methods

### 2.1. Design

This is a mixed-method study involving qualitative co-design workshops with caregivers and HCPs/support workers and a combination of quantitative and qualitative approaches to inform RLO development and evaluation. A mixed-method design enables us to gather comprehensive information from both caregivers and HCPs beyond that which would be possible from a single quantitative or qualitative approach. In addition, the use of qualitative, interactive approaches enables more in-depth and rich data which are complemented by the broader reach of data captured via the survey approaches used. This study does not involve quantitative hypothesis testing and instead involves an exploratory survey approach where sample size calculations have not been conducted. This study will instead aim to recruit a broad representative sample of participants to address the research aim.

The BCW framework [21] and the Behaviour Change Techniques Taxonomy (BCTT) [28] will be utilised to co-create a behaviour change RLO with caregivers, HCPs and support workers. The Am, **S**toryboarding, **P**opulate specification, **I**mplement media, **R**eview and release prototype, **E**valuate (ASPIRE) approach [29] for designing digital education resources will be used, including stakeholder involvement in co-designing the RLO and infographic for HCPs and support workers. As part of the final evaluation step, preliminary summative and formative evaluation of the usability, acceptability and implementation of the RLO and infographic will be undertaken.

Due to the lack of guidelines for the reporting of mixed-method research, the Consolidated Criteria for Reporting Qualitative Research (COREQ) checklist [30] will be followed in conducting and reporting this research.

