## Appendix A

**Table A1 healthcare-12-00029-t0A1:** Survey A1: Usability of the CRIB-RLO.

Part 1 The CRIB-RLO resource ^1^ *Please indicate the extent to which you Agree, are Neutral or Disagree, with the following statements*		
The CRIB-RLO resource held my interest.		
Agree	Neutral	Disagree
2. I enjoyed using the CRIB-RLO resource.		
Agree	Neutral	Disagree
3. I found the CRIB-RLO resource easy to use.		
Agree	Neutral	Disagree
4. The visual elements added to my understanding of the topic.		
Agree	Neutral	Disagree
5. The audio commentaries were engaging.		
Agree	Neutral	Disagree
6. The case studies were engaging.		
Agree	Neutral	Disagree
7. I would prefer to use the CRIB-RLO resource than read written information.		
Agree	Neutral	Disagree
8. It was clear from the learning objectives what was in each section.		
Agree	Neutral	Disagree
9. I would recommend the CRIB-RLO resource to other caregivers or healthcare professionals/support workers.		
Agree	Neutral	Disagree
10. If you Disagree with any of the above statements, please add your suggestions for improving this resource?		
Final Version 1.1, 04/07/2023, IRAS 326807, FMHS 238 0323		

^1^ Questions derived from a survey tool used by: Johnson, S.; Bamber, D.; Bountziouka, V.; Clayton, S.; Cragg, L.; Gilmore, C.; Griffiths, R.; Marlow, N.; Simms, V.; Wharrad, H.J. Improving developmental and educational support for children born preterm: Evaluation of an e-learning resource for education professionals. *BMJ Open*
**2019**, *9*, e029720. https://doi.org/10.1136/bmjopen-2019-029720 [35].

**Table A2 healthcare-12-00029-t0A2:** Survey A2: Impact on caregivers.

Part 1 You			
Please indicate if you are a caregiver or a member of the CRIB public contributors group?			
*Please tick the box*			
Caregiver			
Public contributor			
If you are a caregiver, do you have a child less than one year old?			
Yes			
No			
2. Were you involved in the development of the CRIB-RLO resource?			
Yes			
No			
3. If you would like a link to the final resource please provide your email address below			
Part 2 Your learning			
*Please indicate the extent to which you Agree, are Neutral or Disagree, with the following statements*			
The CRIB-RLO resource has improved my understanding of when my baby is hungry and when they are full.			
Agree	Neutral	Disagree	
2. I am more likely to feed my baby based on their cues or signs than other ways for example, other people’s advice.			
Agree	Neutral	Disagree	

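### The only summative survey for caregivers measures impact, so caregiver acceptability is rated only in a formative prototype survey pooled with professionals

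*Protocol article*

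**What the plan says.** The third objective, at the end of the Introduction, begins "To conduct an initial evaluation of the acceptability of the RLO for caregivers". Section 2.1 (Design) says that "preliminary summative and formative evaluation of the usability, acceptability and implementation of the RLO and infographic will be undertaken". In section 2.3.4, Recruitment for Evaluation states "We will conduct a preliminary evaluation of the functionality, acceptability and usability of the RLO", and Method describes "three online, anonymous surveys evaluating the acceptability and usability of the RLO".

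The survey-specific text differs. Method says that Survey 2 "will ascertain the impact of the RLO on caregivers in terms of changing behaviours related to responsive feeding". Analysis refers to "Survey 2 responses examining the impact and usefulness of the RLO on caregivers". Table A2 in Appendix A is also titled as a survey of impact, and its first learning item reads "The CRIB-RLO resource has improved my understanding of when my baby is hungry and when they are full". The Abstract likewise divides the evaluation into usability, impact on caregivers and implementation.

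The acceptability framework is used only for Survey 3, which goes to professionals. Yet Method says that the framework can be used to evaluate acceptability "by both intervention deliverers and intervention participants".

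**The concern.** The general statements say that the evaluation, including its summative part, covers acceptability and usability. The instrument given to the larger caregiver sample does not carry those constructs. A colleague who follows the plan as written would reach the reporting stage with up to 30 caregivers who had worked through the RLO and had not been asked whether they enjoyed it, found it easy or burdensome, or would recommend it.

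This matters beyond wording. The Discussion expects outputs that are acceptable to caregivers as well as professionals, and presents this work as the step before a randomised trial. Survey 2 is printed in the appendix, so its content is not something left to a longer protocol.

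**Working it through.** No sample size, test or precision target is stated (section 2.1 describes an exploratory survey), so the check is a count and classification of the printed items.

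**Stated counts reproduced.** Table A1 has 9 closed items and one open prompt; the text gives 9 closed. Table A2 Part 2 has 7 closed items; the text gives 7. Table A3 Part 2 has 8 open and 2 closed items; the text gives the same.

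**The surveys side by side** (section 2.3.4 and Appendix A):

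| Survey | Stage | Respondents | Purpose in the specific text | Acceptability or usability items answered by caregivers |
|---|---|---|---|---|
| 1 | Formative, prototype | Up to 20 caregivers, HCPs and support workers together | Usability, content, function | Yes |
| 2 | Summative | Up to 30 caregivers | Impact and usefulness | None of the kinds listed below |
| 3 | Summative | Up to 30 HCPs and support workers | Implementation, built on the acceptability framework | Not given to caregivers |

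**Survey 2 items classified.**
- Understanding: items 1 and 6 (2 items).
- Feeding by cues rather than by other people's advice or product instructions: items 2 and 3 (2 items).
- Confidence in how and when to feed: items 4 and 5 (2 items).
- Motivation: item 7 (1 item).

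The total is 2 + 2 + 2 + 1 = 7. Items on enjoyment, ease of use, burden or recommending: 0 of 7. Table A2 shows no open opinion item either.

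**Can Survey 1 supply the caregiver result?** It has suitable items: interest (1), enjoyment (2), ease of use (3), preference over written material (7) and recommending (9). Two features limit it:
- It rates the prototype, and Analysis says its data are used to find what needs amending.
- Tables A2 and A3 both open with questions about the respondent, but Table A1 as printed has none. The surveys are anonymous, and the article describes no other way to separate caregivers from professionals.

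The number of caregivers among the 20 is also not stated.

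**Can anything else supply it?** The optional feedback form described at the end of Method is for use after the project ends, and its items are not given.

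**The case against.** The strongest reply is that objective 3 asks only for an initial evaluation and does not say it must be summative. Survey 1 goes to caregivers and covers interest, enjoyment, ease, preference and recommending, with an open prompt for suggestions. On this view the sentence about three surveys is loose summary wording, the design is deliberately one instrument per purpose, and rewording one sentence would be enough.

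Much of this stands. A reader might infer that caregiver acceptability is never measured, or that Survey 2 contributes nothing to objective 3. The documents support neither reading. Survey 1 does ask caregivers acceptability-type questions. In Survey 2, items 1, 4, 5, 6 and 7 ask whether the RLO improved understanding, confidence or motivation, which can be read as perceived effectiveness. Method lists effectiveness and understanding within factors found with an adapted version of the acceptability framework.

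Two parts do not stand. First, the article never ties Survey 2 to that framework, and even the generous reading leaves enjoyment, burden and ease of use unasked at the summative stage. Second, Survey 1 cannot give a caregiver-specific answer on its printed form, so rewording alone would leave objective 3 resting on a pooled result.

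A reader might also want the loss expressed as a confidence interval. The documents give neither the caregiver share of Survey 1 nor any expected proportion, so such an interval would rest on invented inputs, and none is offered.

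**Conclusion.** The point holds for summative measurement. Section 2.1 and Method in section 2.3.4 say that acceptability and usability are covered, but the only summative caregiver survey has 0 of 7 items on enjoyment, ease of use, burden or recommending, and at most 5 of 7 that touch on perceived effectiveness. The remaining caregiver evidence is formative, concerns the prototype, and is pooled with professionals in at most 20 responses.

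This rests on the instruments being as printed in Appendix A and on no role information being collected for Survey 1 in some other way. Two details do not alter it. Table A2 lets a respondent tick public contributor, so Survey 2 may not be strictly caregivers only. It also offers a link to the final resource, so Survey 2 respondents may themselves see a version that is not yet final.

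This is a worthwhile and cheap improvement. It does not undermine the impact results that Survey 2 is built to give.

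**What to change.** 1. Add Survey 1 items 2 (enjoyed), 3 (easy to use) and 9 (would recommend) to Part 2 of Survey 2, with the same three response options. One item on time or effort is optional.
2. Add a respondent-role question to Survey 1, so that caregiver and professional answers can be tabulated separately.
3. In Analysis, name the items that answer objective 3 for caregivers.
4. Reword the sentence in Method on the three surveys so that it says which survey measures which construct, and align section 2.1 with it.

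If items cannot be added to Survey 2, make changes 2 to 4 and limit the conclusion on caregiver acceptability to the formative stage.

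The cost is about one more minute per Survey 2 respondent, on a survey expected to take no more than 20 minutes, and a minor amendment to the forms. No change to sample size or analysis method is needed, because frequencies and percentages are already planned.
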